## Methods

### Study design

The study is an open pragmatic cluster randomized trial with before/after measurements and two intervention arms. A cluster design is necessary because randomization is performed on a practice level, the intervention happens on the physician level, but a large part of the data are analyzed at the patient level. The implementation period of the trial is 18 months.

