### Sample size

The project funding agency requires a sample size of at least one-third of the potential PCPs (n = 379), which would capture roughly 2,500 patients with type 2 diabetes mellitus. This sample size allows 80% power (type II error: 0.20) to detect a 20% relative difference between the intervention arms in the proportion of patients achieving a 10% improvement in any one of the following: blood pressure, total cholesterol, or HbA1c (type I error: 0.05; assumed intracluster coefficient 0.6; [67] for calculation methods).

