### Statistical analysis

Statistical analyses will be performed using an intent-to-treat approach with a multilevel model. Linear and generalized linear mixed models will be used to account for the clustered nature of the data, *i.e*., patients clustered within PCPs, and repeated assessments clustered within patients. Such models measure how outcomes change over time within patients and whether these changes depend on patient and/or PCP's characteristics, such as the intervention program or DCT use (see hypothesis two). DCT use is defined as having at least one consultation with a member of the team besides the health psychologist and the traveling educator, which are only available for AQIP patients.

We will use generalized estimating equations (GEE), an extension of the quasi-likelihood approach, to test for differences in the evolution of the primary and secondary endpoints for all patients and within the intervention arms. For binary variables, we use the exponential inverse transformation to obtain the 95% confidence interval for the odds ratio.

Subgroup analyses (see hypothesis one) can distinguish intervention effects using different cut-off values. For HbA1C, three subgroups are defined: patients with HbA1c < 7%; HbA1c ≥ 7% and < 8%; and HbA1c ≥ 8%. For SBP, four subgroups are defined: patients with SBP ≤ 130 mmHg; SBP > 130 mmHg and ≤ 140 mmHg; SBP > 140 mmHg and ≤ 160 mmHg; and SBP > 160 mmHg. For LDL-C, four subgroups are defined: patients with LDL-C < 100 mg/dl; LDL-C ≥ 100 mg/dl and < 115 mg/dl; LDL-C ≥ 115 mg/dl and < 130 mg/dl; and LDL-C > 130 mg/dl.

Linear mixed models with subject-specific intercepts and slopes are used to test whether subject-specific evolutions are related to initial parameters. HbA1c will be transformed logarithmically to meet the parametric assumptions of the statistical models. All analyses will be performed using SAS, version 9.

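### As described, neither the GEE nor the mixed-model route to the arm difference in change allows for change that clusters within physicians or practices

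*Protocol article*

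**What the plan says.** The relevant statements are all in the protocol article.

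- **Study design:** measurements are taken before and after, randomisation is by practice, and "the intervention happens on the physician level".
- **Statistical analysis, mixed models:** the clustering is spelled out as "patients clustered within PCPs, and repeated assessments clustered within patients". These models are to assess "whether these changes depend on patient and/or PCP's characteristics, such as the intervention program or DCT use". For the program, that is the arm-by-time contrast.
- **Statistical analysis, GEE:** GEE is assigned to differences in the evolution of the primary and secondary endpoints. No cluster unit is given there.
- **Abstract, Primary and secondary analysis:** the baseline comparison by GEE takes clustering within physicians into account. The next sentence says the GEE test of evolution accounts for clustering within patients, and mentions neither physician nor practice.
- **Statistical analysis, random slopes:** slopes are named once: "Linear mixed models with subject-specific intercepts and slopes are used to test whether subject-specific evolutions are related to initial parameters".
- **Sample size:** the calculation uses an "assumed intracluster coefficient 0.6" for "the proportion of patients achieving a 10% improvement in any one of the following: blood pressure, total cholesterol, or HbA1c".

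**The concern.** A cluster trial analysed on change needs a variance that reflects how much change itself varies between clusters. Naming PCP as a level does not ensure this. With one value before and one after, a PCP intercept is the same at both times and subtracts out, and so does a patient intercept. A practice intercept would cancel as well, so adding that level alone would not help. What has to be in the model is a cluster-by-time effect, or a variance estimate clustered above the patient.

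The article names neither for the comparison of change. If the analysis were run that way, standard errors would be too small, and AQIP could be declared better than UQIP because some physicians' patients improved together for reasons unrelated to the program.

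**Working it through.** **Inputs.** From Sample size: at least one-third of 379 PCPs, 379/3 = 126.3, and about 2,500 patients, so 2,500/126.3 = 19.8 per PCP. I use 126 PCPs with 20 patients each, balanced. A two-sided 5% test is assumed, as the article does not state sidedness. The intra-PCP correlation of change, ρ, is not given for any analysed endpoint, so it is varied.

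**Why the PCP level drops out.** For patient j of PCP i at time t, with intercepts only:

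Y(ijt) = fixed effects of arm, time and arm×time + b(i) + u(ij) + e(ijt)

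The change is Y(ij1) − Y(ij0) = time + arm×time + e(ij1) − e(ij0). Both b(i) and u(ij) are gone. The arm-by-time test is then a two-sample test on patients' changes, treated as independent.

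**Check by fitting.** Data were simulated for 40 PCPs with 10 patients each, with a PCP-by-time standard deviation of 0.3 and a residual standard deviation of 0.6. The correlation of change is therefore 2×0.09/(2×0.09 + 2×0.36) = 0.18/0.90 = 0.20. In one data set the arm-by-time statistics were:

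| Method | Statistic |
|---|---|
| Mixed model, PCP and patient intercepts | −0.794 |
| Unclustered t-test on changes | −0.794 |
| GEE clustered on patient | −0.796 |
| t-test on PCP mean changes | −0.472 |

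The ratio 0.794/0.472 = 1.68 agrees with the expected √(1 + 9×0.20) = 1.67. Three further data sets showed the same pattern.

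**Type I error at the trial's size.** The design effect on change is 1 + 19ρ, and the actual error of the nominal 5% test is 2[1 − Φ(1.96/√(1 + 19ρ))]. For ρ = 0.05: 1 + 0.95 = 1.95; 1.96/1.396 = 1.404; error 16.0%.

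| ρ | Design effect | Formula | Simulated, continuous | Simulated, PCP mean changes | Simulated, at-target |
|---|---|---|---|---|---|
| 0 | 1.00 | 5.0% | 4.9% | 4.8% | – |
| 0.01 | 1.19 | 7.2% | 7.3% | 5.4% | – |
| 0.02 | 1.38 | 9.5% | 9.7%; 9.8% | 5.2% | 6.6% |
| 0.05 | 1.95 | 16.0% | 17.4%; 15% | 6.0% | 11% |
| 0.10 | 2.90 | 25% | 24.2%; 26% | 4.9% | 15% |
| 0.20 | 4.80 | 37% | 37% | – | 23% |

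Each simulation used 4,000 runs. Two figures in a cell come from two separate sets. In the at-target column ρ is on the latent scale.

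**If practices are larger.** With two PCPs per practice (39.6 patients, an assumption) and the same correlation across the practice, the formula gives 9.6% at 0.01 and 25.2% at 0.05.

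**The protocol's own coefficient.** At 0.6 the design effect with 19.8 patients per PCP is 1 + 18.8×0.6, about 12.3. That leaves 1,250/12.3, about 102 effective patients per arm. The stated 80% power cannot be reproduced, because the reference proportion is not given. It would be reached only if about 75% of the reference arm met the improvement criterion (81%); at 50% the power is 30%.

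**The case against.** The strongest reply is that the article lists levels and does not give a random-effects structure. A three-level model with PCP intercepts and PCP time slopes fits the same sentence, and a condensed article may leave that detail to the full protocol or SAP. This stands. A reader might infer that the mixed models definitely contain no PCP-by-time effect, and that the claim to account for clustering is therefore untrue. The text does not support that much. The subject-specific slopes do not show it either, since that sentence concerns the relation of change to initial values and not the arm comparison.

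The division of work between the two methods is also unclear. The GEE wording could be read as testing change within each arm. In that case the mixed model carries the arm contrast and the question of its by-time term becomes more important.

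Exact cancellation holds for linear models with complete pairs. The primary endpoints are proportions at target, for which it is approximate, and the simulated inflation is smaller. No logistic mixed model was fitted in this check.

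A reader might also put 0.6 into the formula and report an error of about 58%. That coefficient belongs to a composite of 10% improvements that is not an analysed endpoint, so it should not serve as the size of the problem. It shows only that the planners expected an improvement outcome to cluster.

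What the reply does not answer is the Abstract. There the cluster level for the GEE test of evolution is stated, and it is the patient, directly after a sentence that uses the physician level for the baseline comparison. That is more than omitted detail.

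**Conclusion.** The concern holds for the analyses as described. The GEE route is stated to account for clustering within patients only. The mixed-model route, on its natural reading, loses the PCP effect from the before/after contrast. Neither therefore protects the arm comparison of change against clustering within physicians or practices.

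For continuous endpoints the type I error would be about 7% to 25% for correlations of change from 0.01 to 0.10. For at-target indicators it would be about 7% to 15% for latent correlations from 0.02 to 0.10. There is no inflation if change does not cluster. These figures assume balanced PCPs of 20 patients, complete pairs and, for the mixed model, intercepts only. If the full protocol or SAP specifies a cluster-by-time term, the mixed-model part falls away and the Abstract's GEE sentence remains to be corrected.

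**What to change.** In the Abstract (Primary and secondary analysis) and in Statistical analysis, state that:

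1. every mixed model testing arm-by-time includes a random time effect at the randomised practice, and at PCP level where a practice has several PCPs; or, instead, the final value is modelled with baseline as a covariate and a practice random effect, which does not cancel;
2. every GEE test of evolution uses a robust variance clustered on practice;
3. degrees of freedom are based on the number of practices.

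It would also help to say which of the two methods carries the arm comparison for hypothesis one. The cost is an extra random term in the SAS code, a change of cluster unit in the GEE and a sentence or two of text. The confidence interval for the arm difference will be wider wherever change does cluster, with some loss of apparent power.

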**Primary and secondary analysis:**

Statistical analyses will be performed using an intent-to-treat approach with a multilevel model. Linear and generalized linear mixed models will be used to account for the clustered nature of the data, *i.e*., patients clustered withinimary care physicians, and repeated assessments clustered within patients. To compare patient characteristics at baseline and between the intervention arms, the generalized estimating equations (GEE) approach will be used, taking the clustered nature of the data within physicians into account. We will also use the GEE approach to test for differences in evolution of the primary and secondary endpoints for all patients, and for patients in the two interventions arms, accounting for within-patient clustering.

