### Data collection

These practices have no pre-existing registers of diabetic patients. Patients with type 2 diabetes mellitus will be identified using physician memory, searching computerized records, and laboratory lists of patients with increased glycemia or registered glycosylated hemoglobin. Baseline data will be collected over a seven-month period. PCPs will be asked to perform a complete examination and blood analysis at the patient's first visit and to complete a paper form. Identified patients without a visit during the first three months of the project will be invited to participate. The completeness of data capture will be double-checked by a data monitor. Final data will be collected over a seven-month period, with call-backs for non-compliant patients. Patient data sheets include socio-demographic and biomedical data. PCPs will need to indicate whether diabetes is treated by the PCP or in a diabetes clinic.

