### Primary and secondary endpoints

The primary endpoints of the study are the proportion of patients reaching ADA targets for three clinical outcomes: HbA1c < 7%; SBD ≤ 130 mmHg; and LDL-C < 100 mg/dl. Secondary endpoints are the mean improvements in individual values of 12 validated parameters: HbA1c, LDL-C, HDL-C, Total Cholesterol, SBP, DBP, weight, physical exercise, healthy diet, smoking status, and statin and anti-platelet therapy.

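### The arm effect is tested as a difference in change, with baseline entered as an outcome; adjusting the final result for the measured baseline would usually be more precise and needs no new data

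*Protocol article*

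**What the plan says.** The Study design section describes a cluster randomized trial with measurements before and after, so each patient has one baseline and one final assessment. The Statistical analysis section plans linear and generalized linear mixed models with assessments nested in patients and patients nested in physicians. It says that these models show how outcomes move over time and "whether these changes depend on patient and/or PCP's characteristics, such as the intervention program or DCT use". The abstract adds that GEE will be used to "test for differences in evolution of the primary and secondary endpoints for all patients, and for patients in the two interventions arms".

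Under Primary and secondary endpoints: "The primary endpoints of the study are the proportion of patients reaching ADA targets for three clinical outcomes", namely HbA1c, systolic pressure (read here as the achieved value) and LDL-C. The secondary endpoints are mean improvements.

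The baseline values exist on their measured scale. Under Data collection, "PCPs will be asked to perform a complete examination and blood analysis at the patient's first visit and to complete a paper form".

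Two other uses of the starting value appear in the Statistical analysis section: subgroup bands of HbA1c, SBP and LDL-C, and linear mixed models that relate patients' slopes to their initial values. No sentence adjusts the overall arm comparison for the measured baseline.

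**The concern.** When both assessments are outcomes and each arm has its own baseline mean, the program effect is the arm-by-time term. That term subtracts the whole baseline difference between arms. Baseline adjustment subtracts only the part that predicts the final result, which in a randomised comparison is normally more precise.

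The primary endpoints lose further information because their baseline is cut at the target. In the main arm comparison, a patient starting at HbA1c 7.1% and one starting at 11% both enter simply as off target, although their chances of finishing on target differ.

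At stake is precision on all three primary endpoints. With about 126 physicians, a chance imbalance at baseline is also realistic. Given such an imbalance, regression to the mean flatters the arm with the worse start when change is compared.

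**Working it through.** **Inputs from the article (Sample size).** Recruitment is "at least one-third of the potential PCPs (n = 379), which would capture roughly 2,500 patients with type 2 diabetes mellitus". Hence 379/3 is about 126 physicians, with about 2,500/126 = 19.8 patients each and 1,250 per arm if allocation is equal. Also "type I error: 0.05; assumed intracluster coefficient 0.6". Two-sided testing is assumed. The article gives neither a baseline-to-final correlation nor a control proportion, so both are varied below.

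**The plan's own power figure.** It reads "This sample size allows 80% power (type II error: 0.20) to detect a 20% relative difference between the intervention arms", and the quantity is a difference "in the proportion of patients achieving a 10% improvement in any one of the following: blood pressure, total cholesterol, or HbA1c". The design effect is 1 + 18.8 × 0.6, about 12.3, leaving 1,250/12.3, or about 102 effective patients per arm. For a final-value comparison, a 20% relative difference then has power of 21% (40 vs 48%), 30% (50 vs 60%) and 44% (60 vs 72%). It reaches 80% only near a control proportion of 75%. The stated 80% therefore cannot be reproduced without an unstated input. It also concerns a different, improvement-type endpoint, so it is not used as the base here.

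**Variance of the two analyses.** Let r be the correlation between the baseline and final values (cluster means in a cluster analysis), with equal variances.
- Difference in change: proportional to 2(1 − r).
- Baseline-adjusted: proportional to 1 − r².
- Ratio, adjusted to change: (1 − r²)/[2(1 − r)] = (1 + r)/2.

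If the change analysis has 80% power, its expected z is 1.96 + 0.84 = 2.80, and adjusted power is Φ(2.80/√[(1+r)/2] − 1.96).

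| assumed r | variance ratio | variance saved | adjusted power | gain (points) |
|---|---|---|---|---|
| 0.3 | 0.65 | 35% | 93.5% | 13.5 |
| 0.5 | 0.75 | 25% | 89.9% | 9.9 |
| 0.7 | 0.85 | 15% | 86.0% | 6.0 |
| 0.8 | 0.90 | 10% | 84.0% | 4.0 |
| 0.9 | 0.95 | 5% | 82.0% | 2.0 |

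**Dependence on the base.** With the article's ICC of 0.6 and r = 0.5, power (change vs adjusted) is 14.7 vs 18.2% at a control proportion of 30%, 21.0 vs 26.5% at 40%, 30.1 vs 38.3% at 50% and 44.4 vs 55.6% at 60%. The gain is 3.5 to 11 points.

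**Dependence on physician stability.** At ICC 0.6 with 20 patients per physician, r between cluster means is (0.6s + 0.4w/20)/(0.6 + 0.4/20). Here s is the stability of the physician effect over time and w the within-physician patient correlation, both assumed. With w = 0.5, s = 0.5 gives r = 0.50 and s = 0.8 gives r = 0.79.

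**Simulation of the binary case.** There were 126 clusters of 20, with a latent normal measure cut at the target (ICC on the latent scale). Effects were set for roughly 80% power in the change analysis, with 700 runs for power and 400 under no effect. Both analyses were logistic models with cluster-robust errors: arm-by-time on target status, against final target status adjusted for the measured baseline and its cluster mean.

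| ICC | s | w | on-target proportion | power, change | power, adjusted | equivalent variance ratio |
|---|---|---|---|---|---|---|
| 0.05 | 0.8 | 0.5 | 50% | 76.3% | 90.6% | 0.68 |
| 0.05 | 0.8 | 0.7 | 40% | 80.3% | 92.1% | 0.71 |
| 0.10 | 0.8 | 0.5 | 40% | 76.6% | 88.9% | 0.70 |
| 0.60 | 0.8 | 0.5 | 50% | 78.9% | 87.6% | 0.82 |
| 0.60 | 0.95 | 0.5 | 50% | 75.1% | 82.7% | 0.81 |

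Type I error ranged from 4.8 to 7.0% for change and from 2.8 to 6.2% for adjusted, near 5% given the number of runs.

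**A limiting case.** At ICC 0.6 and s = 0.95, a purely linear adjustment for the continuous cluster mean gained nothing (variance ratios 1.04 and 1.07). Linear adjustment for the individual baseline alone did worse (1.10 and 1.28). The form of the adjustment therefore matters.

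**The case against.** The strongest objection is that the article names model families and clustering levels but gives no equation. A repeated-measures model with baseline means held equal across arms fits the same words and would recover the efficiency, and covariate lists commonly sit in an analysis plan that is not shown. Part of this stands: the loss is conditional on free baseline means. But the article does state the contrast, a difference in evolution, and does not state that constraint. For the binary endpoints, the constrained model would still use only on/off baseline status.

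Second, the starting level is not ignored. The subgroup bands and the slope models use it. That is true, and a reader should not infer that baseline severity plays no part in the plan. Neither use adjusts the overall arm effect.

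Third, the secondary endpoints are defined as mean improvements, so a change analysis matches its own definition. It is a valid estimator, and the issue is precision only.

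Three stronger readings are tempting, and the documents do not support them:
- *That the planned estimate is biased.* Over-correction holds only given a chance baseline imbalance. Averaged over randomisations both analyses are unbiased, and simulated type I error is near 5%.
- *That adjustment can never be less precise.* This needs a baseline common to the arms and untouched by allocation, and adjustment on the same measure in a suitable form. Randomization follows recruitment and physicians are unblinded. Baseline is collected over seven months, with patients found partly from memory or by new screening. The article does not say that every baseline value precedes allocation.
- *That a fixed number of power points is lost.* If 80% is instead taken as the power of a final-value comparison, power (change vs adjusted) is 66 vs 84%, 80 vs 90% and 95 vs 98% at r of 0.3, 0.5 and 0.7: gains of about 18, 10 and 2 to 3 points. No single narrow range covers these.

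**Conclusion.** The point holds as one of efficiency. As written, and unless baseline means are constrained equal, the arm comparison is a difference in change that uses the primary endpoints' baseline only as target status. Adjustment lowers the variance by 35% to 15% for r of 0.3 to 0.7, worth roughly 13 to 6 power points where the change analysis has 80%, and 4 to 2 points at r of 0.8 to 0.9. All these correlations are assumptions.

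At the article's ICC of 0.6, the gain turns on how stable physician effects are. The logistic adjustment with individual and cluster-mean baseline gained about 8 to 9 points in the two cases simulated, while purely linear adjustment could gain nothing. The plan is valid without the change, but the improvement is worth making.

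**What to change.** For each primary endpoint, make the arm comparison a model of final target status on arm, adjusted for the patient's baseline value of the same measure on its continuous scale (log HbA1c, SBP, LDL-C) and for its cluster mean, within the clustered model already planned. Report marginal proportions or a risk difference beside the odds ratio. For the continuous secondary endpoints, compare final values between arms adjusted for baseline. Keep the evolution model as descriptive.

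The cost is a wording change and no new data. The odds ratio becomes conditional on baseline, which is why the marginal result should accompany it. Missing baselines need a simple stated rule. The gain relies on baseline values not being affected by allocation, so the text should say whether they are recorded before the physician learns the arm.

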### Scientific hypothesis

One hypothesis is that an advanced quality improvement program (AQIP) significantly improves clinical outcomes in persons with type 2 diabetes compared to a usual quality improvement program (UQIP). Subgroup analyses can analyze the effect of the program in the two intervention arms using cut-off values. The second hypothesis is that persons with type 2 diabetes who make use of a DCT will have significantly better outcomes compared to non-users of the DCT, regardless of their intervention arm.

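### The subgroup cut-offs are the primary-endpoint thresholds, so before/after change in at-target status within a baseline subgroup cannot show where the program works; compare AQIP with UQIP at follow-up instead

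*Protocol article*

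**What the plan says.** All places are in the protocol article.

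- **Primary and secondary endpoints.** The primary endpoints are proportions at target: "HbA1c < 7%; SBD ≤ 130 mmHg; and LDL-C < 100 mg/dl" (SBD is evidently systolic pressure). Secondary endpoints include mean improvement in the same three values.
- **Statistical analysis, subgroups.** "For HbA1C, three subgroups are defined: patients with HbA1c < 7%; HbA1c ≥ 7% and < 8%; and HbA1c ≥ 8"%. The other two sets begin "For SBP, four subgroups are defined: patients with SBP ≤ 130 mmHg" and "For LDL-C, four subgroups are defined: patients with LDL-C < 100 mg/dl", each followed by three higher bands. That makes 3 + 4 + 4 = 11 subgroups. Their stated use: "Subgroup analyses (see hypothesis one) can distinguish intervention effects using different cut-off values". The paragraph names no classification time, outcome or model.
- **Statistical analysis, models.** Mixed models describe change within patients and whether it depends on the program. GEE is used "to test for differences in the evolution of the primary and secondary endpoints for all patients and within the intervention arms", with odds ratios for binary variables. No follow-up-only comparison is described.
- **Scientific hypothesis.** Hypothesis one compares AQIP with UQIP, then adds: "Subgroup analyses can analyze the effect of the program in the two intervention arms using cut-off values". That sentence can be read as an effect within each arm or between arms.

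**The concern.** The lowest cut in each set is the endpoint's own threshold. Forming subgroups on the baseline value therefore fixes the baseline value of the binary endpoint for that parameter. A reader who carries the evolution analysis into the subgroups, as the text invites, meets one of two problems: an odds ratio that does not exist, or a change in proportion that can only go one way. Patients selected as controlled can only lose control, and patients selected as uncontrolled can only gain it.

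These subgroups are meant to show where the program works. The likely misreading is deterioration in controlled patients and improvement in uncontrolled patients, seen in both arms, taken as a program effect when ordinary visit-to-visit variation produces the same pattern.

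**Working it through.** The article gives no figure for the subgroup analyses, so there is none to reproduce. Its 80% power statement concerns the whole trial and does not enter here.

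**1. Baseline status (no assumptions beyond baseline classification).** HbA1c < 7% is both the endpoint and the lowest subgroup, so that subgroup is 100% at target and the other two are 0%. The same holds for SBP at 130 mmHg and LDL-C at 100 mg/dl. All 11 subgroups are fixed at 100% or 0%. Only the parameter that defines the subgroup is fixed; status on the other two endpoints is free.

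**2. Logistic before/after model.** The time log odds ratio is logit(final proportion) − logit(baseline proportion). With a baseline proportion of 0 or 1, the second term is −∞ or +∞. The time-by-arm term is a difference of two such infinities. In a simulated HbA1c 7–8% subgroup, the ordinary logistic time coefficient was 5.8, 10.8, 20.8 and 25.8 after 5, 10, 20 and 30 iterations, with standard errors of 0.8, 9.7, 1,440 and 17,545. GEE robust standard errors were undefined. The same model fitted normally in all patients.

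**3. Change in the at-target proportion with no program effect.** Assumptions, none from the article: bivariate normal values with equal means before and after; HbA1c 7.1 (SD 1.2), SBP 138 (SD 16), LDL-C 105 (SD 33); correlation ρ. The expected follow-up share at target is P(final at target | baseline in subgroup). The rejection columns are for one arm of independent patients, using an exact paired (McNemar) test at 0.05 in 300 runs, with HbA1c mean 7.2 and SBP mean 137 and otherwise the same values. The sample of 102 is roughly the effective number per arm at the article's intracluster coefficient: one third of 379 is about 126 physicians; 2,500/126 = 19.84 patients each; 1 + 18.84 × 0.6 = 12.3; 1,250/12.3 ≈ 102.

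| Baseline subgroup | At target, baseline | Follow-up, ρ 0.7 | Follow-up, ρ 0.9 | Rejects: n 1,250, ρ 0.7 | n 1,250, ρ 0.9 | n 102, ρ 0.7 |
|---|---|---|---|---|---|---|
| HbA1c < 7 | 100% | 73.0% | 84.7% | 1.00 | 1.00 | 0.99 |
| HbA1c 7–8 | 0% | 34.0% | 22.7% | 1.00 | 1.00 | 0.95 |
| HbA1c ≥ 8 | 0% | 9.7% | 0.9% | 1.00 | 0.04 | 0.03 |
| SBP ≤ 130 | 100% | 64.0% | 79.5% | 1.00 | 1.00 | 0.98 |
| SBP 130–140 | 0% | 30.4% | 23.5% | 1.00 | 1.00 | 0.84 |
| SBP 140–160 | 0% | 10.1% | 1.8% | 1.00 | 0.81 | 0.17 |
| SBP > 160 | 0% | 0.9% | 0.0% | 0.00 | 0.00 | 0.00 |
| LDL-C < 100 | 100% | 71.6% | 83.9% | 1.00 | 1.00 | 0.99 |
| LDL-C 100–115 | 0% | 38.9% | 31.4% | 1.00 | 1.00 | 0.72 |
| LDL-C 115–130 | 0% | 23.7% | 8.5% | 1.00 | 1.00 | 0.17 |
| LDL-C > 130 | 0% | 8.2% | 0.6% | 1.00 | 0.01 | 0.01 |

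In all patients at n = 1,250 and ρ = 0.7 the same test rejects in 2–5%. A hand check explains the pattern. Within a subgroup every switch goes the same way, so k switches give p = 2 × 0.5^k. Five give 0.0625 and six give 0.031, so six patients crossing the threshold suffice. In HbA1c 7–8% at ρ = 0.7, about 1,250 × 0.307 × 0.340 ≈ 130 per arm would cross. In SBP > 160 it is about 1,250 × 0.085 × 0.009 ≈ 1.

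A second simulation used both arms together, 126 clusters, an assumed intracluster correlation of 0.05 and a cluster-robust test of change. It rejected in about 100% of runs in all 11 subgroups at ρ = 0.5 and in 10 of 11 at 0.7 (SBP > 160: 11%). At 0.9 it rejected in 100% of runs in 8 of 11 (HbA1c ≥ 8: 72%; highest LDL-C: 42%; SBP > 160: 0%).

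**4. Continuous values.** Expected change with no effect is −(1 − ρ)(subgroup mean − overall mean). For HbA1c ≥ 8 at ρ = 0.7: −0.3 × (8.69 − 7.1) = −0.48, rejected in 100% of runs. For LDL-C 100–115: −0.3 × (107.46 − 105) = −0.74, rejected in about 12% (6–14% across the correlations tried). The model fits, but away from the mean its change is still regression to the mean.

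**5. Arm contrast at follow-up.** With no effect, comparing final at-target status between arms rejected in 3–8% of runs in 10 of 11 subgroups at ρ = 0.7 and in 9 of 11 at 0.9. It was lower (0–2%) where almost nobody reaches target. Fitted log odds ratios were finite: 0.21 (SE 0.14) for HbA1c 7–8% and −0.15 (SE 0.13) for HbA1c < 7%.

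**The case against.** The strongest reply is that the article never assigns the before/after logistic model to the subgroups. The GEE sentence covers all patients and the arms. The subgroup paragraph is permissive and names no model, and mean changes in the continuous values are also planned and can be fitted. Hypothesis one compares arms, and regression to the mean acts alike on randomised arms. On this view only detail is missing, and an article may leave detail to the full plan.

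Much of this stands. A reader might infer that the planned subgroup analysis cannot be fitted at all, that its time test falsely rejects everywhere, and that the randomised comparison within subgroups is lost. The text does not support any of these:

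- The failure to fit is conditional on baseline classification and on the binary endpoint of the subgrouping parameter.
- A model without finite estimates gives no usable time test. The rejections above come from paired or change-in-proportion tests that the article does not name, so the two problems are alternatives and do not occur together.
- Rejection is not universal: at ρ = 0.9 and 1,250 per arm, three of the 11 subgroups reject in 4% of runs or fewer.
- The arm contrast is recoverable. With baseline status constant in both arms it reduces to final status.

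What the reply does not remove is the combination. The article itself fixes the thresholds, the identical cut-offs and a framework of change over time, and words the subgroup aim in a way that permits a within-arm reading. That is more than an omitted detail.

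**Conclusion.** The concern holds in conditional form. With baseline subgroups, at-target status on the subgrouping parameter is 100% or 0% at baseline in all 11. Evolution of that endpoint within a subgroup then either has no finite odds ratio or mostly measures regression to the mean. These two facts follow from the stated thresholds and from ordinary variation between visits.

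The sizes depend on the assumed means, SDs and correlations. With 1,250 per arm, the subgroups on either side of each threshold reject in essentially all null runs. With 102 per arm they reject in 72–99% at ρ = 0.7 and 53–75% at ρ = 0.9. The extreme subgroups at high correlation often do not reject. The point concerns how the subgroup results would be read; the main AQIP versus UQIP comparison is unaffected.

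**What to change.** In Statistical analysis:

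- State that subgroups are defined by the baseline value.
- For each primary endpoint, fit one logistic model to final at-target status, allowing for clustering as planned, with arm, baseline category and their interaction. Report the AQIP versus UQIP odds ratio with 95% confidence interval in each category.
- For continuous values, compare follow-up between arms adjusted for baseline.
- Rest any claim that the effect differs between categories on the interaction.
- Tabulate before/after change within categories descriptively, and do not present it as a program effect.
- Assign LDL-C of exactly 130 mg/dl, which the printed bands leave out.

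In Scientific hypothesis, reword the subgroup aim as the effect of AQIP versus UQIP by baseline category.

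The cost is wording only, with the same data and software. The one loss is that within-subgroup before/after p-values are no longer reported. Where almost nobody reaches target, the arm contrast will be imprecise and should be presented as such.
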